## Abstract

**Background:**

International consensus shows that community-based rehabilitation (CBR) service is an effective way to improve functioning and negative symptoms and address the treatment gap for schizophrenia. Rigorous trials are needed in China to demonstrate effective and scalable CBR interventions to significantly improve outcomes for people with schizophrenia and to provide evidence of the economic benefits. The objectives of this trial are to examine the effectiveness of CBR as an adjunct to test the usual facility-cased care (FBC) in comparison to FBC alone in improving a range of outcomes in people with schizophrenia and their caregivers.

**Methods:**

This trial is a cluster randomized controlled trial design in China. The trial will be conducted at three districts of Weifang city, Shandong province. Eligible participants will be identified from the psychiatric management system where community-dwelling patients with schizophrenia have been registered. Participants will be recruited after providing informed consent. 18 sub-districts will be randomly allocated in a 1:1 ratio to facility-based care (FBC) plus CBR (intervention arm) or FBC alone (control arm). The structured CBR intervention will be delivered by trained psychiatric nurses or community health workers. We aim to recruit 264 participants. The primary outcomes include symptoms of schizophrenia, personal and social function, quality of life, family burden of caring, etc. The study will be conducted according to good ethical practice, data analysis and reporting guidelines.

**Discussion:**

If the hypothesized clinical benefit and cost-effectiveness of CBR intervention are confirmed, this trial will provide significant implications for policy makers and practitioners to scale up rehabilitation services, as well as for people with schizophrenia and their family to promote recovery and social inclusion, and to alleviate the burden of care.

**Trial registration:**

Chinese Clinical Trial Registry (ChiCTR2200066945). Registered December 22, 2022.

## Background

Schizophrenia is a major severe mental disorder that has profound adverse effects on individuals and poses huge disease burden to families [1]. It usually has an onset in early adulthood and is often accompanied with persistent or relapsing symptoms. According to the estimation of the Global Burden of Disease Study, globally, schizophrenia accounted for 6.51 million DALYs in 2017, representing 0.51% of the all-cause DALYs [2]. Despite its low prevalence, the mortality rate of people with schizophrenia is two to three times higher than that in the general population [3]. And most people with schizophrenia have difficulties with work and social participation. In China, 6 million individuals suffer from schizophrenia: 80% of them with moderate to severe disability; 40% of them have never received treatment [4, 5]. Such high risk of disability among schizophrenic patients and consequent adverse outcomes, which are likely due to extremely low access to psychiatric services, has made schizophrenia a priority public concern in recent years.

International consensus shows that community-based rehabilitation (CBR) service, as a broader supportive approach, is an effective way to improve functioning and negative symptoms and address the treatment gap for schizophrenia [6]. In particular, the WHO’s mhGAP guidelines and the third edition of the Word Bank’s Disease Control Priorities (DCP3) both recommended that community-based rehabilitations as an adjunct to antipsychotic treatment for schizophrenia [7]. The rehabilitation interventions, which can be implemented by trained community workers, are more needful in low- and middle-income countries due to the shortage of psychiatrists and psychiatric services [8]. These interventions have been proven to be effective and acceptable to address the broader social and livelihood needs of service users in some low- and middle- income countries (LMICs), such as India [9] and Ethiopia [10].

Community-based mental rehabilitation has received high-level attention from Chinese national policy makers recently. China’s first Mental Health Law, which was enacted in 2012 and enforced in 2013, requested to provide mental rehabilitation services to psychiatric patients. The Strategic Plan for Healthy China 2030 issued in 2016 clearly stated the mission of “equal access to rehabilitation services for all disabled persons”. Suggestions on Accelerating the Development of Community-based Rehabilitation Services among People with Mental Disorders issued in 2017, provided specific steps to implement and scale up community-based rehabilitations: 80% of counties (districts) can provide mental rehabilitation services and 60% of patients with mental disorders can receive these services in 2025.

However, there is a lack of high-quality study on how to effectively implement community-based rehabilitation interventions for schizophrenia, and to conduct the health economic evaluations for the interventions in China, which weakens evidence base for policymaking. Therefore, rigorous trials are needed in China to demonstrate effective and scalable interventions to significantly improve outcomes for people with schizophrenia and to create evidence of the economic benefits of these interventions, for use in advocacy with the government to establish national programs. This paper presents the protocol for community-based rehabilitation interventions on quality of care for people with schizophrenia in China (CRISC) project, which is a cluster randomized trial that evaluating the effectiveness of CBR intervention.

## Objectives

The objectives of the trial are: first, to examine the effectiveness of CBR as an adjunct to test the usual facility-cased care (FBC) in comparison to FBC alone in improving a range of outcomes in people with schizophrenia and their caregivers at 12 months and, second, to determine if the CBR intervention is cost effective in China.

The primary objectives of the trial are to determine whether the FBC + CBR intervention will be more effective than FBC alone in:

i)reducing symptoms of schizophrenia at 12 months;ii)improving physical function and quality of life for people with schizophrenia over 12 months, and.iii)reducing the burden of caring for caregivers of people with schizophrenia at 12 months.

The secondary objectives are to determine whether, FBC + CBR will be superior to FBC alone, in:

i)improving adherence to antipsychotic treatment at 6 months and 12 months,ii)reducing the hospital readmission rate at 6 months and 12 months for people with schizophrenia, and.iii)improving the knowledge about schizophrenia of people with schizophrenia and their caregiver at 6 months and 12 months.

## Methods

### Study design

The design is a cluster randomized controlled trial with sub-district as the unit of randomization. There are mainly three reasons for choosing cluster randomization as the method of randomization: (1) CBR was provided as group intervention at community healthcare, which exclude the possibility of randomization at individual level; (2) randomization at sub-district will be more economical and less time-consuming for both provider and participants; (3) The acceptability will be maximized, and the possibility of contamination could be minimized if all participants in a sub-district are allocated to either intervention or control arms. The study flow chart is presented in Fig. 1. Eighteen sub-districts from three district in Weifang, Shandong province were included for the trial, 9 will be randomly allocated to the intervention arm (FBC plus CBR) and 9 randomly allocated to the control arm (FBC alone). In total, 334 participant dyads (patients and their caregivers) will be recruited, with 18.6 participant dyads on average recruited for each sub-district.

**Fig. 1 Fig1:**
[figure not shown]
CRISC flow chart

### Setting

The trial will take place in Hanting, Kuiwen and Weicheng district, Weifang city, Shandong province in China. The three districts have a population of 1,470,000 persons in 23 sub-districts. Six sub-districts in each district were chosen, yielding to 18 sub-districts in the trial. There is a community health center in each sub-district that covering the facility-based care of local people with severe psychiatric disorders including schizophrenia. The number of registered schizophrenia patients of each sub-district ranges from 52 to 138, with 12 to 25 patients are planned to recruit.

### Participant inclusion criteria

The inclusion criteria for participating in the trial are: (1) Be aged 18–59 years; (2) Have a primary diagnosis of schizophrenia by psychiatrists according to ICD-10 DCR criteria; (3) Have had the an illness duration of at least 12 months; (4) Be residing within the sub-district for the next 12 months; (5) Have never been diagnosed with severe physical conditions, drug or alcohol dependence, organic brain disease, learning disability or hearing impairment; (6) Have a primary caregiver who is willing to participate in the study; and (7) being in stable conditions and community -dwelling. The exclusion criteria are: (1) being hospitalized due to schizophrenia at the time of recruitment; (2) being illiterate or physically incapable of text or verbal communication.

### Participant flow

#### Participant identification

In China, most of the community-dwelling patients with schizophrenia who have been diagnosed in hospitals or primary care services are registered in the National Information System for Psychosis of China. The recruitment processes of this trial are as follows: Primary care physicians from 18 sub-districts of Hanting, Kuiwen and Weicheng districts, identify the potential participants who met the inclusion criteria from their local registered community-dwelling patients with schizophrenia. Eligible patients will be invited to join the trial by primary care physicians or nurses. They will be given information about the trial and the study procedure in a way appropriate to the participants’ literacy level by telephone or face-to face. Those who consent (or, for those without decision-making capacity, the caregiver will consent on their behalf) to participate will go to community health care center to sign the informed consent and complete baseline data collection. Within each sub-district, the recruitment will continue until approximately 20% of community-dwelling patients have been recruited.

#### Allocation

The randomization processes of sub-districts to intervention and control arms are as follows: (1) The sociodemographic characteristics and specific information of patients with schizophrenia of each sub-district will be obtained from the information system [11]; (2) A pairwise matching work will be conducted to identify 9 pairs of matched sub-district that share similar characteristics (number of population, prevalence of schizophrenia, average income per capita, etc.); (3) Within each pair, one sub-district will be randomly assigned into intervention arm, and the remaining one will be assigned into control arm, yielding to 9 sub-districts in intervention arm that providing FBC + CBR, and 9 sub-districts in control arm with FBC only. The sub-district allocation list will be kept securely on a password-protected document by the trial coordinator. To reduce selection bias, the potential eligible participants will not be informed about the allocation of their sub-district until they have consented to participate and baseline data of all participants have been collected. Recruitment and participant flow will be closely monitored by the trial coordinator.

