##### CBR delivery

The CBR intervention will be delivered by group at community health centers. Two CBR workers will be attached to each sub-district and have one group of 10–20 people with schizophrenia. CBR delivery will commence immediately after recruitment into the trial. A total of 18 group intervention sessions will be implemented within the following 12 months, and each group intervention session will last 90–120 min. The intervention is delivered in two phases (Table 1): In phase 1 (intensive engagement phase), 12 intervention sessions will be delivered fortnightly during the first 6 months. The content of the intervention includes a series of modules such as developing a positive therapeutic alliance, understanding schizophrenia, adherence management, etc. (Table 1). In phase 2 (stabilizing phase), 6 intervention sessions will be delivered monthly during the last 6 months. Intervention modules in this phase are similar with phase 1 to reinforce the progress, and the content will include more in-depth discussion and address unmet needs from the first phase. In this phase, a personal rehabilitation plan for each participant will be generated to help their continued rehabilitation at home.

The content and process of the phase specific delivery of the intervention has been manualized. CBR workers will be closely supervised at each site by psychiatrists who will work as designated intervention coordinators. They will coordinate the overall delivery of the intervention and assure the quality and fidelity of the intervention at the site. The treating psychiatrists will provide clinical leadership for the community care teams and ongoing supervision to maintain safety and quality standards.

In total, we anticipate that each participant in the intervention arm will receive a maximum of 18 group-based rehabilitation sessions during the 12 months of the intervention. In evaluating the intervention, a minimum adequate number of 12 sessions attended over 12 months was set according to priori definitions.

**Table 1 Tab1:** CRISC community-based rehabilitation (CBR) intervention outline

phase	months	frequency	Objectives	CBR Modules	CBR activity

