To maintain blinding of these assessments, the primary care physicians and psychiatrists who administered the outcome measures will be independent of the CBR intervention. The primary care physicians were unable to be blinded to the allocation of treatment since they were the coordinator to contact the participants from their local sub-districts. The psychiatrists, who will assess the main primary outcomes (symptoms of schizophrenia and personal and social function), will be blinded to the allocation of treatment. Since neither the participant nor the family caregivers will be blind to their allocation status at the time of the 6 and 12 month interviews, we intend to minimize the chances of unmasking during the outcome assessments by instituting the following measures: (1) the intervention team and data collection teams at the sites will not have any interactions during the trial; (2) the data collection team are told that they are evaluating two interventions that is unknown about which one is better; (3) orient the participants and their caregivers prior to each assessment that they should not disclose whether or not they are attending CBR.

**Table 2 Tab2:** Summary of outcome measures

Outcomes (Intermediate outcome)	Interviewees	Assessment scale	Month 0 (Baseline)	Month 6 (Intermediate)	Month 12 (Endline)

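### The stated safeguard against selection bias withholds allocation from patients only; nothing says that the physicians and nurses who recruit are kept unaware of the arm

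*Protocol article*

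**What the plan says.** All references are to the protocol article.

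- **Allocation.** Sub-districts are matched into nine pairs on registry data, and one of each pair is randomised to the intervention arm. The measure offered against selection bias is that "the potential eligible participants will not be informed about the allocation of their sub-district until they have consented to participate and baseline data" have been gathered for all participants. On custody: "The sub-district allocation list will be kept securely on a password-protected document by the trial coordinator". The section gives no date for the draw and does not say what recruiters know.
- **Participant identification.** Primary care physicians of the 18 sub-districts "identify the potential participants who met the inclusion criteria from their local registered community-dwelling patients with schizophrenia". Then: "Eligible patients will be invited to join the trial by primary care physicians or nurses". Within each sub-district, "the recruitment will continue until approximately 20% of community-dwelling patients have been recruited". No order of approach is given.
- **Setting.** "The number of registered schizophrenia patients of each sub-district ranges from 52 to 138, with 12 to 25 patients are planned to recruit".
- **Outcome assessment.** "The primary care physicians were unable to be blinded to the allocation of treatment since they were the coordinator to contact the participants". The psychiatrists who rate PANSS and PSP (the Personal and Social Performance Scale) are to be blinded.
- **Data management and analysis.** The 12-month PANSS total is adjusted for baseline PANSS and site.
- **CBR delivery.** "CBR delivery will commence immediately after recruitment into the trial".

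**The concern.** Randomising sub-districts balances the sub-districts. It protects the comparison of patients only if the patients in each are chosen without regard to the arm. In this trial the people who choose are local clinicians, and the Outcome assessment section describes them as familiar with their patients. They are therefore well placed to guess who will attend group sessions or do well. The inclusion criterion of being in a stable condition has no threshold in the article, so eligibility itself leaves some room for judgement.

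The safeguard is aimed at the patients, but the risk lies with the recruiters. If a physician or nurse knows that the sub-district will provide community-based rehabilitation (CBR), promising candidates may be approached first. In a control sub-district there is no such incentive. The resulting difference between arms would look like a treatment effect, and the analysis could correct only the part captured by measured baseline variables.

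**Working it through.** **1. What recruiters can know, from the text.**

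| Question | Answer in the article | Section |
|---|---|---|
| Who identifies candidates? | Local primary care physicians | Participant identification |
| Who invites? | The same physicians, or nurses | Participant identification |
| Who is not told the arm until baseline is done? | Potential participants | Allocation |
| Who holds the list? | The trial coordinator, under password | Allocation |
| Are the physicians blinded? | No, because they contact participants | Outcome assessment |
| Are the nurses blinded? | Not addressed | – |
| When is the draw made? | Not stated | – |

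A promise to withhold allocation until baseline is complete has a purpose only if an allocation may exist before then. The reason given for not blinding the physicians is their contact role, and they also have that role in recruitment. Knowledge of the arm at recruitment is thus a reasonable inference, although no sentence states it.

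**2. The recruitment fraction.** Assume that the smallest register goes with the fewest recruits and the largest with the most. Then 12/52 = 23% and 25/138 = 18%, which agrees with the stated 20% or so. These are shares of registered patients *recruited*. The number eligible and the number invited are not given, so the size of the pool open to discretion cannot be computed.

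**3. What a residual selection difference would do.** The documents give no figure for such a bias, so this step is an illustration.

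Inputs from the article:
- 220 participants required before attrition (110 per arm), ICC 0.05 and alpha 0.05 (Sample size estimation);
- 18 sub-districts (Study design).

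Assumptions: a two-sided test, equal cluster sizes, the ICC applied at sub-district level, a normal approximation, no gain from matching or baseline adjustment, and no true effect.

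- Mean cluster size m = 220/18 = 12.22.
- Design effect = 1 + (12.22 − 1) × 0.05 = 1.561.
- Effective number per arm = 110/1.561 = 70.5.
- Standard error of the arm difference = √(2/70.5) = 0.168 SD.

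With a residual selection difference b, in SD units, the type I error is P(|Z + b/0.168| > 1.96):

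| b (assumed) | b/SE | Type I error |
|---|---|---|
| 0 | 0 | 5% |
| 0.1 SD | 0.59 | about 9% |
| 0.2 SD | 1.19 | about 22% |

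For scale, the difference detectable with 90% power at this size is (1.960 + 1.282) × 0.168 = about 0.55 SD. A larger trial does not help. A smaller standard error makes b/SE larger, so the same bias would raise the type I error further.

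**The case against.** The strongest reply is that nothing says allocation precedes recruitment. Allocation is described after identification, and the sentence on unblinded physicians sits in a paragraph about those who administer outcome measures. If the draw in fact came last, there would be no problem. This is fair as far as it goes: recruiters' knowledge of the arm is inferred. But the article does not say that the draw comes last, and its promise to withhold allocation suggests otherwise.

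Other points on that side stand in whole or in part:

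- **The list is controlled.** Password protection with the coordinator is a real restriction on access, so a reader should not infer that silence towards patients is the only protection. It is still not a statement that recruiters are unaware.
- **Four in five patients passed over.** A reader might infer from the 20% target that about 80% of registered patients are never invited. The text does not support this. The target concerns those recruited, and the remainder includes ineligible patients and refusals.
- **Mitigation exists.** Baseline PANSS enters the primary model. Perceived social support, adherence, illness knowledge and caregiver burden are also measured at baseline, and sensitivity models may add characteristics that differ between arms. Social support is therefore not wholly unmeasured. Motivation and expected attendance are not among the listed measures, and the additional adjustment is not primary. Blinded raters protect the rating of PANSS and PSP, not the choice of patients.
- **Start of CBR.** Starting immediately after recruitment could be read as contradicting the wait for all baselines. Because CBR is delivered to an assembled group and baseline is part of the recruitment visit, the two can be read together. This is loose wording at most.
- **Detail left to a full protocol.** Order of invitation may be such a detail. The direction of the safeguard is not: the article states it, and it leaves out the recruiters.

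**Conclusion.** The concern holds as a risk built into the design. The stated safeguard covers patients, the recruiters are not said to be unaware of the arm, and the physicians among them are described as unblinded because of their contact with participants. Recruitment carried out as written is open to selection by arm.

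The documents do not support the stronger reading that physicians knew the arm when they invited patients, or that selection took place. The rise in type I error to about 9% or 22% rests on assumed biases of 0.1 and 0.2 SD and on the standard error of 0.168 SD. It shows how vulnerable the comparison would be and is not an estimate of the bias to expect. The point merits correction because such a bias cannot be fully repaired in the analysis and is cheap to prevent.

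**What to change.** 1. Keep the registry matching, but draw each pair's allocation only after both of its sub-districts have completed recruitment and baseline. State this sequence in the Allocation section, so that no physician, nurse or coordinator can know the arm while recruiting.
2. Invite eligible registered patients in a computer-generated random order until the quota is met.
3. Record and report the numbers eligible, invited and consenting by sub-district and arm.
4. Align the wording on the start of CBR in the CBR delivery section with the Allocation section.

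If allocation has already been drawn, state the actual sequence and who knew the arm at recruitment, and report the same counts by arm so that readers can judge the risk.

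The cost is a short wait for the slower sub-district of each pair. No extra participants are needed. The added delay should be small, because allocation is already to be withheld from patients until all baseline data are in.
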